#### Sexual and reproductive health package

PtC participants are offered a comprehensive SRH package of services, in line with those described for the FASTPrEP study [21]. These services include family planning (pregnancy testing, contraceptive counselling, and contraceptive administration) and testing or screening (resource-dependent) and treatment for sexually transmitted infections (*Chlamydia trachomatis*,* Neisseria gonorrhoea*,* and syphilis).* All participants are further screened for alcohol misuse (AUDIT scoring system), mental health (Patient Health Questionnaire (PHQ-4), and tuberculosis (TB) symptoms. Referral pathways are in place following positive HIV or pregnancy tests, positive TB screening, detection of intimate partner violence, and for high AUDIT or PHQ-4 scores.

### Data collection, safety, and ethical oversight

Potential participants are invited to undergo an informed consent process, that covers their participation in both the FASTPrEP project and the PtC study. As this study concerns use of PrEP as part of SRH services, participation assumes ongoing sexual activity and all PrEP products and SRH services offered are approved for use and the majority are available in public healthcare settings for minors (< 18 years). Since this is health research, participation amongst minors (aged 15–17 years old) is usually restricted by the need for parental/guardian consent. Given the need to reduce barriers to participation a parental consent waiver has been obtained and is available for participants aged 15–17 years old that allows them to self-consent for participation in the study. Parental involvement and disclosure is encouraged.

Potential participants are screened for co-enrolment in other HIV related clinical trials in the area using the nationally accredited Biometric Co-Enrolment Prevention System (BCEPs), which requires biometric registration. Once co-enrolment is excluded, participants have their biometrics registered on a separate participant tracking system that creates a unique participant profile and allows participants to move freely between PtC/FASTPrEP service sites [21]. 

All study data, including the informed consent forms, is captured directly onto an online REDCap system by study staff (including recruiters, counsellors, clinicians, and research assistants) at the time of data reporting. Demographic, behavioural (including sexual behaviour), and clinical information (including medical history, obstetric history where applicable, use of sexual and reproductive health services, HIV testing, and PrEP use) are collected at each study visit. Point of care and laboratory results are captured as they become available to the unique participant REDCap profile. A return visit auto-calculator that can calculate the date of return for PrEP continuation is built into the REDCap database. This calculator allows for manual adjustment to account for participant schedules and holidays and aids clinicians in accurately informing participants of their return dates.

### Study reimbursement

To simulate a real-world environment where PrEP is delivered within a standard service of care from public health care facilities, no reimbursement for inconvenience (such as time spent or transport) is offered to participants who participate in this study. The SRH service package and PrEP modalities are, with the exception of CAB-LA, part of the existing public healthcare service in SA. Participants that are invited to and attend research visits for additional questionnaires, in-depth interviews, and focus group discussions are provided with R150 ($8.50) per visit. No post-trial access to injectable PrEP product is provided at the end of the study, however, the study team is committed to advocating for the incorporation of injectable PrEP products into standard of care services. Oral and DapiRing PrEP products are already available for free through standard of care service provision in government clinics. At the end of the study, participants that remain interested in PrEP use will be transitioned into the public healthcare PrEP service. Clinical trial insurance has been obtained.

#### Statistical analysis

PrEP initiation in this study is defined as having received a 28-day regimen of oral PrEP tablets, receiving a DapiRing, or receiving a CAB-LA injection depending on the respective product choice. Initiators are participants that have selected a specific PrEP product at baseline after receiving PrEP choice counselling.

To determine the primary and secondary endpoints of short-term and durable persistence (as defined above), a Cox proportional hazards model to estimate the hazard of discontinuing PrEP at 7 months and through 18 months will be conducted, thus taking into account the presence of censoring due to end of study period or drop-out, including all participants who are confirmed as HIV-uninfected at enrolment and who attend at least the PrEP initiation visit (visit 1).

More specifically, PrEP persistence at 7 and 18 months will be summarized in the first instance as proportions of subjects on a given modality at those time points out of those who started on the modality and compared using a chi-square test. Additionally, Kaplan-Meier curves will illustrate the time to discontinuation by PrEP modality. Cox proportional hazards model will be used to analyse the risk of discontinuation overall, (i) regardless of modality and (ii) taking modality into account. Frailty models will account for repeated discontinuations per subject. Modality will be included as a time-varying exposure variable. Additionally, time to switching modality will be analysed using a Cox proportional hazards model, with frailty terms to account for repeated switches, if required. Models will include subject-specific characteristics that may confound the association between modality and risk of discontinuation. Different subgroups (adolescent girls and young women, intimate male partners, and gay and other men who have sex with men) can be included as a predictor in the models and additionally analysis will be repeated for sub-groups of interest. The average time to restart, the mean number of restarts for a participant and the total number of restarts across the study period will be reported and used to describe the variation in PrEP user journeys throughout the product.

Deeper understanding of the PrEP user experience will be drawn from self-administered questionnaires (n = up to 180 randomly selected participants at month 0, 6, and 12) and in-depth interviews (IDI) with a sub-set of PrEP providers and PrEP users. Survey data will be summarised and described. IDI’s will be audio-recorded, translated (with independent back-translation for verification), and transcribed for analysis. The recordings will be reviewed and verified for accuracy by the interviewers. Transcripts will then be translated and key quotations back-translated to verify meaning. A subset of 20% of transcripts will be double-coded to examine the inter-rater reliability of the coding process. After coding, investigators will search by substantive codes and themes identified utilising matrices to organize and allow for comparisons by group (e.g., PrEP users: age, PrEP product selected at baseline, PrEP product switching, partner status; and PrEP provider: age, site of PrEP distribution, PrEP product administered). Patterns in the matrices will be used to identify themes. Tables of themes will be created using the verbatim quotations as evidence to support the themes that serve as the primary data analyses approach. Conclusions will be based on interpretation of these tables of themes with quotations. Data will be managed using NVivo Software (QSR International). Changes in PrEP user and PrEP provider perspectives over the 6-month period (collectively and across matched individual) will be quantified to identify changes pre- and post- CAB-LA experience at the user or provider level, with McNamara’s test for matched pairs used to determine significance.

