## Study design

PtC seeks to describe patterns of persistence of HIV PrEP products, individually and overall, amongst a cohort of South African adolescents and youth (aged 15–29 years) when offered different PrEP modalities (oral vs. DapiRing vs. injectable) within a sexual and reproductive health service (SRH) package and supported by comprehensive choice counselling. PtC will probe implementation barriers and enablers in PrEP adoption (decision to use any PrEP product), initiation (first dose of any PrEP product), and persistence amongst both PrEP users and PrEP providers (specialised nurses and HIV counsellors) in real-world government primary health care facilities and mobile clinic settings. PtC utilises a hybrid implementation design with co-primary implementation and clinical aims, in the form of a non-randomised, quasi-experimental trial design.

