### Aims and objectives

The primary clinical aim of PtC is to describe patterns of short and long-term persistence (as measured over 7 months and 18 months respectively) across three HIV PrEP products, individually and overall, amongst a cohort of South African adolescents and youth. Participants are offered a choice between PrEP products, following HIV testing and comprehensive choice counselling. PrEP products include (a) oral PrEP (Emtricitabine/tenofovir), prescribed as a daily tablet or for event-driven use for select male participants; (b) a Dapivirine-containing vaginal ring (DapiRing) that requires monthly replacement, for non-pregnant and non-breastfeeding adolescent girls and young women; and (c) Cabotegravir long-acting (CAB-LA) as a two monthly intra-muscular gluteal injection.

PrEP persistence is defined as sustained, continuous use of the selected product as intended, with consideration of both (a) a < 7-day gap in PrEP availability for daily dosing (oral PrEP), DapiRing insertion, or subsequent injection or (b) a < 28-day gap. The 7-day gap between the scheduled return vs. actual return is consistent with the definitions used in CAB-LA phase 3 clinical trials [17]. – [18] The 28-day gap follows South African recommendation guidelines for a “missed visit” and is the clinical time point where re-initiation on CAB-LA would be needed. In the South African context, it is expected that the 28 day gap will provide a more realistic timeframe for return. In addition to a missed visit, non-persistence on a specific product is further defined as any participant that switches to using another PrEP product with (a) < 7 days and (b) < 28-day gap between products. PrEP persistence in the cohort, by product and on PrEP overall, will be calculated and reported at 7 months (short-term persistence) and 18 months (long term persistence). The comparison of PrEP persistence by product will be related to the hypothesis that there will be a significantly greater persistence in the CAB LA group compared to oral PrEP and/or DapiRing.

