Participants may be naïve to PrEP use, using PrEP through government PrEP services, or they may be recruited from an existing and affiliated large-scale PrEP programme in the study area (“FASTPrEP”), which operates four mobile clinics, a PrEP depot site, as well as from all public health clinic facilities in the study area [21]. FASTPrEP is a novel demonstration project designed to introduce, scale up, and evaluate current (oral PrEP and DapiRing) provision through differentiated models of service delivery that integrates PrEP into a comprehensive SRH package [21]. Enrolment on PtC for non-FASTPrEP participants necessitates simultaneous co-enrolment on FASTPrEP. PtC is promoted at all existing FASTPrEP sites and through its existing social media platforms.

*Sample size calculation*: With 900 participants who start CAB-LA, the study will have > 85% power to detect an 8% or greater difference in PrEP persistence at 7 months comparing oral PrEP users to injectable PrEP or injectable vs. DapiRing selectors using a simple chi-square test. We conducted a sensitivity analysis to estimate the power with different levels of sample size at 95% confidence interval. If a lower sample size were reached, we would have > 80% power to detect a 11% difference or more with 700 participants in CAB-LA vs. 200 in oral PrEP. Study enrolment will cease once a minimum of 900 participants have self-selected to initiate on CAB-LA at baseline, irrespective of the number of oral PrEP and DapiRing users at that time point.

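### Oral and ring users continuing their own product count as starters beside CAB-LA users new to theirs, so the unadjusted persistence comparison is open to prevalent-user bias of unknown direction

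*Protocol article*

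**What the plan says.** **Who counts as a starter.** The Statistical analysis section gives the operational rule: "PrEP initiation in this study is defined as having received a 28-day regimen of oral PrEP tablets", or receipt of a ring or a CAB-LA injection. It adds: "Initiators are participants that have selected a specific PrEP product at baseline after receiving PrEP choice counselling". Neither sentence asks whether the participant was already using that product.

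**Who can enrol.** Under PrEP users, participants may be naïve to PrEP, "using PrEP through government PrEP services, or they may be recruited from an existing and affiliated large-scale PrEP programme in the study area". That programme, FASTPrEP, exists to "introduce, scale up, and evaluate current (oral PrEP and DapiRing) provision through differentiated models of service delivery". The Setting section says both study sites were picked because they had many oral PrEP users in the year before. The Study reimbursement section lists CAB-LA as the one modality outside public care.

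**What is compared.** The hypothesis under Aims and objectives is that "there will be a significantly greater persistence in the CAB LA group compared to oral PrEP and/or DapiRing". Persistence is first summarised as "proportions of subjects on a given modality at those time points out of those who started on the modality" and compared by chi-square, with Kaplan-Meier curves by modality. The sample size paragraph bases power on a simple chi-square test. Table 1 counts 7 and 18 months from PrEP initiation. For the Cox models: "Models will include subject-specific characteristics that may confound the association between modality and risk of discontinuation". Prior PrEP use is not named.

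**The concern.** Someone already established on tablets who receives another month's supply at visit 1 enters the oral group as a starter, with the clock set to zero at that resupply. If early stopping is common, this person has already come through it. The CAB-LA group has no counterpart, because hardly anyone can arrive already on CAB-LA. For some oral and ring users the comparison then measures persistence from an arbitrary point in an ongoing course. For CAB-LA users it measures persistence from first use of the product.

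The unadjusted chi-square carries the power statement and is the first reported test of the product hypothesis. If prior use is unevenly spread and predicts persistence, the observed difference reflects that mix as well as the product.

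**Working it through.** **1. The plan's own figure.** For a two-sided 5% test of two proportions with p̄ the pooled proportion:

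SE0 = √[p̄(1−p̄)(1/n1+1/n2)], SE1 = √[p1(1−p1)/n1 + p2(1−p2)/n2], power = Φ[(|p1−p2| − 1.96·SE0)/SE1].

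The only scenario with both group sizes is 700 CAB-LA vs 200 oral, 11 points, power above 80%. The document gives no base rate. Power is 81.5% at a comparator rate of 30%, 78.6% at its lowest (about 45%) and 83.1% at 60%, so the figure reproduces to within 2 points. The 8-point figure (above 85% with 900 on CAB-LA) has no stated comparator size. With an assumed 600 comparators and 50% vs 42%, power is 86.2%.

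**2. Who falls where under the written rule.**

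| At entry | Chooses | Counted as | New to that product? |
|---|---|---|---|
| Naïve | any | starter | yes |
| On oral PrEP | oral | oral starter | no |
| On ring | ring | ring starter | no |
| On oral PrEP or ring | CAB-LA | CAB-LA starter | yes, but PrEP-experienced |

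Rows 2 and 3 have no CAB-LA equivalent. Row 4 shows that CAB-LA can still contain PrEP-experienced people.

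**3. Size if only the oral group is affected (assumed).** Let q be the share of oral starters already on oral PrEP and d their excess 7-month persistence. Oral persistence rises by q·d. For q of 10–50% and d of 10–30 points, that is 1 to 15 points. Starting from 50% vs 42%, 900 vs 600:

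| q | d | Oral, pooled | Observed gap | Power |
|---|---|---|---|---|
| 10% | 10 | 43% | 7 | 75.9% |
| 10% | 20 | 44% | 6 | 62.6% |
| 25% | 20 | 47% | 3 | about 21% |
| 40% | 20 | 50% | 0 | 5% |

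**4. Size if CAB-LA also contains experienced users.** With share c and the same d, the net shift towards oral is d(q − c). At d = 20:
- q = 10%, c = 30%: 20 × (−0.20) = −4 points, favouring CAB-LA.
- q = 50%, c = 10%: 20 × 0.40 = +8 points, favouring oral.
- q = c: zero.

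**5. What simple exclusion would do.** Take q = c = 25%, d = 20 and no true difference (42% among new starters in both groups). Pooled, both groups stand at 42 + 0.25 × 20 = 47%, and the test rejects 5% of the time. Drop continuing users from oral only: oral falls to 42% with 600 × 0.75 = 450 people, while CAB-LA stays at 47% with 900. Then p̄ = (423 + 189)/1350 = 0.4533, SE0 = 0.02874, SE1 = 0.02860, and (0.05 − 0.05633)/0.02860 = −0.221. The rejection rate is about 41%, towards the hypothesis.

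**6. What stratification would do.** Take q = 25%, c = 10%, d = 20, 900 vs 600. The naïve stratum is 810 vs 450 and the experienced stratum 90 vs 150. With no true difference, the pooled test compares 42 + 2 = 44% with 42 + 5 = 47% and rejects about 21% of the time. The strata compare 42% with 42% and 62% with 62%, so the stratified test keeps 5%.

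With a true 8-point difference, the pooled gap is 52 − 47 = 5 points, power about 48%. For Cochran-Mantel-Haenszel, the weights w = n1·n2/(n1+n2) are 289.3 and 56.25, and the summed difference is 0.08 × 345.5 = 27.64. The null SE is √(Σ w·p̄(1−p̄)) = √(72.09 + 12.80) = 9.21, and the alternative SE is √(71.13 + 12.35) = 9.14. (27.64 − 1.96 × 9.21)/9.14 = 1.05, so power is about 85%. The naïve stratum alone (810 vs 450) has about 78%.

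**The case against.** **The aim is descriptive and real-world.** The study follows a cohort offered choice, and every product's clock starts at the same event: selection after counselling. Including experienced users fits that purpose. This stands, and is why nobody should be removed. It does not cover the comparative hypothesis or the test that carries the power.

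**The Cox model is named as the analysis for the endpoints and may adjust for prior use.** This stands in part. A covariate list is commonly left to an analysis plan, so its absence is not the point here. What the article does fix is the starter definition and an unadjusted chi-square and Kaplan-Meier comparison on it, and Cox covariates do not touch those. In a self-selected cohort, prior use is also only one confounder among several.

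**A reader might infer that the plan contradicts itself on initiation.** The Study design section speaks of "PrEP adoption (decision to use any PrEP product), initiation (first dose of any PrEP product", and an existing oral user's resupply is not a first-ever dose. But that gloss can equally mean the first product received in the study. Read as first-ever PrEP, it would also exclude oral-experienced CAB-LA users. The documents do not establish a contradiction.

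**A reader might infer that the plan hides a CAB-LA advantage.** That needs c to be well below q. No section gives either share, and site selection on past oral volume does not show how many current users choose tablets again once injections are offered. Nor does the article say that continuing users persist better. That is plausible, but it is an assumption.

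**A reader might conclude that the comparison should be restricted to people new to their product.** Step 5 shows why that is unsafe: it leaves experienced users in CAB-LA only.

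**Conclusion.** The point holds as a vulnerability in the main unadjusted comparison. It is certain from the text that current oral and ring users may enrol, that they count as starters when resupplied, and that CAB-LA starters are in practice all new to that product. It follows that the 7- and 18-month chi-square and Kaplan-Meier comparisons can reflect the mix of prior users as well as the product.

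Neither size nor direction can be fixed from the document. Under the assumed 20-point effect of experience, illustrative mixes shift the difference between −4 and +8 points, against a design difference of 8; with equal shares there is no shift. The power figures also assume 600 comparators and 50% vs 42% persistence. The change is worthwhile because it is cheap and protects against bias either way.

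**What to change.** - Keep all participants and the stop at 900 CAB-LA starters.
- At baseline, classify each participant by prior PrEP use: none; another product; same product within the previous 28 days (the protocol's own gap for CAB-LA re-initiation). State where lapsed users of the same product go; they belong with the PrEP-experienced.
- Report the 7- and 18-month proportions and Kaplan-Meier curves by this class within product.
- Replace the simple chi-square for the product comparison by one stratified on PrEP-naïve versus PrEP-experienced, for example Cochran-Mantel-Haenszel. Treat the naïve stratum as the like-for-like comparison of new starters: the experienced stratum still sets people continuing a product beside people switching to CAB-LA, so step 6 holds there only if experience acts alike whichever product it was with.
- Name prior PrEP use as a covariate in the Cox models.
- Do not simply drop same-product users from the oral and ring groups.

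Cost: one derived baseline variable and some extra tables. PrEP use is already collected at each visit (Data collection, safety, and ethical oversight). Precision within strata is lower: in the step 6 example, about 78% power in the naïve stratum alone against about 85% for the stratified test.

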#### PrEP choice counselling

 The PrEP choice counselling script was co-created through two formative workshops, one with PrEP-experienced health care providers and administrators (*n* = 25) and one with members of the FASTPrEP youth reference committee (*n* = 10). Feedback from these workshops, alongside choice counselling literature and South African national recommendations for CAB-LA counselling, was used to create the first version of the script, which is delivered using a motivational interviewing approach [22]. The counselling process is monitored through quarterly fidelity checks with opportunity for iterative adjustments based on feedback from the fidelity visits and the counsellors. The aims of the counselling session (which were created during the formative workshops) are firstly, to provide comprehensive information about each PrEP product, and secondly, to empower the PrEP user to contextualise that information within their own lifestyles and sexual practises.

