#### Setting

Participants are recruited from the Mitchells Plain-Klipfontein health-sub-district in Cape Town, South Africa. Demand creation for PrEP is currently ongoing in this district under the FASTPrEP programme, whereby the communities are exposed to PrEP educational materials and encouraged to visit community and public health sites to access SRH services, including PrEP [21]. While the FASTPrEP project operates from several mobile, clinical, and community sites (including schools), this study operates from a single mobile and a single clinic site. These sites were selected based on a record of high numbers of oral PrEP users during the preceding year of FASTPrEP implementation and support from local district health officials. The overall model of differentiated PrEP service delivery is outlined in Table 3.

The mobile setting is a Desmond Tutu Health Foundation run mobile clinic that comprises of trained research staff who follow research-specific protocols with resources afforded to them by the research project budget. The primary aim of this site is SRH services and associated research activities. The government health clinic is a government primary health care facility comprising of government clinical and administrative staff, with support from PtC research staff embedded on-site (including a research assistant, HIV counsellor, and two peer navigators), and which follows national, provincial, and local healthcare delivery guidelines and is limited by the resources available to the state. The primary focus of this clinic is healthcare delivery, including services beyond SRH such as antenatal care, HIV treatment, and a midwife obstetric unit. There are minor differences in clinic flows between the sites which have potential to differentially influence the participant experience of the study, PrEP choice counselling, and PrEP administration.

**Table 3 Tab3:** Differentiated service delivery of PrEP choice

	Oral PrEP	Vaginal PrEP	Injectable PrEP
Where (Service Location)	Mobile clinic Government health clinic		
Who (Service Provider)	NIMART-qualified nurses (with medical officer oversight) Lay counsellors Peer Navigators		
When (Service Frequency)	At initiation – one month supply given After 1 month – 3 month supply given	At initiation – one month supply given After 1 month – 3 month supply given	Initiation doses: At initiation and one month Maintenance doses: Every 8 weeks

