## Discussion

The PtC study is evaluating the real-world implementation of PrEP choice, with the first-time inclusion of three approved PrEP products. The protocol was specifically designed to simulate a realistic context for PrEP roll-out, with the aim to firstly, evaluate persistence with expanded PrEP choice and secondly, describe practical challenges that may occur when recruiting young people into HIV prevention services, providing PrEP choice counselling, initiating PrEP, and supporting PrEP continuation.

These aims are supported by the inclusion of two types of settings, mobile clinics and primary health care facilities. Mobile clinics are capable of reaching participants in community spaces (such as malls, sports grounds, and transport hubs), offer a tailored and efficient health services, and can be designed to be adolescent friendly. These attributes partially overcome some of the well-described challenges of primary health care clinics [21]. However, mobile services in this study are also staffed by teams that may be better resourced (in terms of staff, equipment, and support) and more familiar with research than in clinic settings. This may falsely elevate PrEP outcomes in this setting, compared to a more traditional government setting. The government primary health care facilities are small clinics with limited resources and staffing, that provide a limited primary care service that includes SRH and HIV treatment and care. Some of the barriers to services in this environment have been reported to include long waiting times, unfriendly staff attitudes, high staff turnover, and medication stock outs [1, 3]. However, the vast majority of PrEP choice in SA will be delivered from such facilities which therefore provide a realistic view of PrEP implementation challenges.

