## Limitations

This study has several limitations. Firstly, while an extensive effort will be made to simulate real-world conditions, there are some aspects of the clinical trial setting that cannot be avoided. This includes oversight from highly qualified and trained study staff members that may offer a higher level of specialized care than what is provided in public healthcare settings where staff turnover may be high. PtC staff members are specifically trained in adolescent and youth friendly service provision and will undergo gender sensitization training, which is not necessarily part of standard of care training packages. Secondly, the PtC counselling intervention assumes the continuous availability of an experienced HIV counsellor, which is not always the case in primary healthcare settings where counsellors may also often see high staff turnover. Thirdly, the mobile clinic and government primary health clinic site are likely to have notable differences including the number of study support staff and the focus of the service, with the mobiles offering a targeted SRH service and the clinic supporting multiple diverse primary care services. Outcomes that may be influenced by these differences will be formally tested for in the study analysis.

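### The product comparison is not tied to study site, although the protocol says site may influence both choice counselling and PrEP outcomes

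*Protocol article*

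**What the plan says.** The Statistical analysis section of the protocol article first summarises persistence at 7 and 18 months as proportions by starting product, "compared using a chi-square test". The sample size paragraph is built on the same simple test. Kaplan-Meier curves, Cox models and frailty models follow. The adjustment sentence reads: "Models will include subject-specific characteristics that may confound the association between modality and risk of discontinuation". Population subgroup is named as a possible predictor; site is not.

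On site, the article makes these statements:

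- Setting: "this study operates from a single mobile and a single clinic site". Differences in clinic flow between the two are called minor, but are said to "have potential to differentially influence the participant experience of the study, PrEP choice counselling, and PrEP administration".
- Discussion, on the better-resourced mobile teams: "This may falsely elevate PrEP outcomes in this setting, compared to a more traditional government setting".
- Limitations, after listing the mobile/clinic differences: "Outcomes that may be influenced by these differences will be formally tested for in the study analysis".
- Table 1, Adoption endpoint: the proportions reached and sustained are compared between mobile and government sites.
- Table 3: all three products are offered at both sites.

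**The concern.** Product is self-selected after counselling, so any factor that shifts both product choice and persistence will distort the product contrast. The article places site on the outcome side, as a possibility. It also places site next to the exposure side, because counselling is the step at which the product is chosen. If one site retains people better and also starts a larger share of them on CAB-LA, a crude comparison credits the site's performance to the injection. A Cox model without site does the same. If the imbalance runs the other way, a true CAB-LA advantage is hidden.

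The stated hypothesis in Aims and objectives is greater persistence on CAB-LA than on oral PrEP and/or the ring, so the bias would bear on the main clinical claim. Testing whether outcomes differ by site, as Limitations promises, does not remove site from the product contrast.

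**Working it through.** **The plan's own figure.** The article states more than 85% power for an 8-point difference with 900 CAB-LA starters, using a simple chi-square test. It gives neither the comparator size nor the base rate. With two-sided alpha 0.05, 900 vs 900 gives 92.5% to 99.6% power over comparator persistence of 20% to 80%. With 900 vs 450, power is about 79% to 83% for comparator persistence of 30% to 60%. The figure can be met, but cannot be confirmed or refuted. It is used here only as the yardstick of 8 points.

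**Inputs for the site bias.** The documents give no persistence by site and no product mix by site. All of the following are assumptions:

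- equal enrolment at the two sites;
- no product effect within either site;
- oral and ring pooled as the comparator;
- persistence pm (mobile) and pc (clinic);
- CAB-LA shares sm (mobile) and sc (clinic).

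**Formulas.**

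- Crude CAB-LA persistence = (sm·pm + sc·pc) / (sm + sc)
- Crude comparator persistence = [(1−sm)·pm + (1−sc)·pc] / [(1−sm) + (1−sc)]

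Example: (0.8×0.6 + 0.6×0.4)/1.4 = 0.514, and (0.2×0.6 + 0.4×0.4)/0.6 = 0.467. The difference is 0.048, which is 60% of the 8-point target.

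| CAB-LA share, mobile/clinic | Persistence, mobile/clinic | CAB-LA | Others | Spurious difference |
|---|---|---|---|---|
| 85% / 65% | 60% / 40% | 51.3% | 46.0% | 5.3 points |
| 80% / 60% | 60% / 40% | 51.4% | 46.7% | 4.8 points |
| 85% / 65% | 55% / 45% | 50.7% | 48.0% | 2.7 points |
| 80% / 60% | 55% / 45% | 50.7% | 48.3% | 2.4 points |
| 75% / 70% | 60% / 40% | 50.3% | 49.1% | 1.3 points |
| 75% / 70% | 55% / 45% | 50.2% | 49.5% | 0.6 points |

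**Effect on the test.** In the 80%/60%, 60%/40% case, 900 CAB-LA starters imply 900 × 0.3/0.7 ≈ 386 others. The standard error is √[0.25 × (1/900 + 1/386)] = 0.0304, so the expected z is 0.0476/0.0304 = 1.57. A nominal 5% test then rejects about 35% of the time with no product effect.

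An equivalent form of the bias is (a − b) × (pm − pc), where a and b are the mobile shares among CAB-LA starters and among comparators. With mean persistence of 50% and 450 or 900 comparators:

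| a / b | Site gap in persistence | Bias | Rejection, 450 to 900 comparators |
|---|---|---|---|
| 60% / 50% | 10 points | 1.0 point | 6% to 7% |
| 60% / 40% | 20 points | 4.0 points | 28% to 40% |
| 70% / 40% | 20 points | 6.0 points | 55% to 72% |
| 70% / 30% | 20 points | 8.0 points | 79% to 93% |

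**After stratifying by site.** Within each site the expected difference is zero by construction, so the test rejects at about 5%.

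**Precision cost, same 80%/60%, 60%/40% case.** With N participants in total, the unstratified variance is 0.25/(0.7×0.3×N) = 1.190/N. The stratified variance is 0.24/(0.20×N) = 1.200/N, where 0.24 = 0.6×0.4 in each site and 0.20 is the mean of 0.8×0.2 and 0.6×0.4. The increase is about 0.8%.

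**The case against.** The strongest reply is that this is a covariate missing from one paragraph of a condensed article. The adjustment sentence gives no list, so age, sex and prior PrEP use are not named either, and the list may sit in an analysis plan that is not shown. Initiation site is a fixed value for each participant and could be read as covered by the article's criterion of potential confounding. The chi-square is a first summary followed by adjusted models. Limitations also shows that the authors have site in view.

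Much of this stands. A reader might infer that the plan adjusts for participant characteristics alone and shuts site out. The text does not say so; it simply does not name site. A reader might also infer that the protocol declares site a confounder. It does not: it describes minor differences with a potential effect and outcomes that might be raised, and never says that product mix differs by site.

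The same caution applies to enrolment period. The counselling script is monitored "with opportunity for iterative adjustments based on feedback from the fidelity visits and the counsellors", and changes in ring approval and oral guidelines are anticipated. But no section says that period affects persistence, the expected ring approval concerns pregnant and breastfeeding women, the expected guideline change concerns event-driven dosing that the study already promotes, and enrolment closes for all products together. A period effect would be conjecture.

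What the reply does not answer is that the named first-line test, on which the study is sized, adjusts for nothing. The Limitations sentence neither promises nor rules out adjustment of the product contrast. Leaving that open is avoidable, given what Setting and Discussion say about site.

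**Conclusion.** The point holds as an inexpensive improvement to the stated analysis. The first product comparison is unadjusted, and the models are not said to carry site, while the article itself describes site as a possible influence on counselling and on outcomes. Bias arises only if persistence and product mix both differ by site, and the documents report neither. Its direction is therefore unknown.

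Under the assumed inputs the spurious difference is about 0.6 to 5.3 points against the 8-point design difference. The upper end needs 20-point gaps between sites in both persistence and CAB-LA share; milder gaps give 0.6 to 2.7 points. It is tempting to conclude that site alone could produce the whole target difference. That would need something like mobile shares of 70% vs 30% together with a 20-point persistence gap, and nothing in the documents supports imbalances of that size. These sizes refer to the comparison of proportions; no figure was derived for the Cox hazard ratios.

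**What to change.** In the Statistical analysis section:

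1. Replace the plain chi-square comparison of products with a Cochran-Mantel-Haenszel comparison stratified by initiation site (mobile vs clinic), or report it alongside.
2. Include initiation site as a stratum or covariate in the Cox and frailty models that take modality into account, and say that this is how the site differences raised in Setting, Discussion and Limitations enter the product comparison.
3. Define site as the site of PrEP initiation, because the data collection section lets participants move freely between service sites.

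Calendar period of initiation is at most an optional covariate in a sensitivity analysis.

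The cost is analysis wording. Site must already be recorded for the Table 1 Adoption endpoint, it has two levels, and every product is offered at both. The loss of precision was about 0.8% of the variance in the worked case.
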